#### Sensitivity analyses

There will be two planned sensitivity analyses. The first sensitivity analysis will compare participants who attend at least 75 % (9/12) of treatment visits to the wait-list control group to gain an estimate of efficacy versus effectiveness. If there are any cases removed from analysis due to a high influence on the mixed effects model (cooks distance > 4/n) [77], a sensitivity analysis will also be performed to compare the results of the mixed effects model with and without highly influential points included.

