### Sample size

The sample size necessary for a randomized controlled trial with three repeated measures at 0, 7 and 18 weeks was calculated using online sample size software (GLIMMPSE 2.0) using methods detailed by Muller et al. [37–39]. The calculation was performed using a significance level of 0.05, a power of 0.8, a minimum detectable mean difference between groups of 10 points on the Short Musculoskeletal Function Assessment Dysfunction Index (SMFA-DI) [40] at both 7 weeks and 18 weeks, and a standard deviation at each time-point of 23 points on the SMFA-DI based on baseline data from a series of 20 people with chronic pain referred to physiotherapy at WACHC. The calculations were made assuming a correlation between baseline and 7 weeks of 0.84, a correlation between baseline and 12 weeks of 0.82, and a correlation between 7 weeks and 18 weeks of 0.84, based on the same clinical population. The needed sample size calculated was 88 participants. To account for a potential 20 % drop-out rate, the investigators will recruit 110 participants (n = 55 in each group).

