### Withdrawing participants from this study

Participants may withdraw from the treatment at any time. Participants who choose to withdraw will be documented, and data will be analyzed as a member of the group to which they were randomly assigned.

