### Analysis

Statistical analysis will be conducted using Stata software, version 13 (StataCorp, College Station, TX, USA). Baseline characteristics for both treatment and wait-list groups will be presented as means and standard deviations for normal data, and medians and interquartile range for non-normal data, and number of patients and percentages for categorical data. Between-group comparisons will be made for baseline data using a Student’s *t*-test for continuous data and Chi squared or Fisher’s exact test for categorical variables to determine the results of the randomized allocation.

To address objectives #1 and 2, between-group differences in change in primary (SMFA-DI) and secondary outcomes will be analyzed using linear mixed-effects modelling with repeated measures at 0, 7, and 18 weeks. A *P* value of less than 0.05 will be considered indicative of statistical significance for all comparisons. The minimum changes required for the change to be considered clinically meaningful for each scale are listed in Table 1. An advantage of using linear mixed-effects modelling is the ability to utilize all available data points without multiple imputation when there are multiple missing data points [75]. Between-group comparisons will be limited to data collected before the 18-week assessment time point due to anticipated carry over effects due to the long-term changes in function associated with exercise approaches for people with chronic pain [19, 20]. Analysis will use intention-to-treat principles.

To address objective #3, a within-group analysis in the wait-list group will be performed comparing the change in function during the treatment period (weeks 18 to 36) to the change in function during the wait-list period (weeks 0 to 18) using a mixed effects model. If there is no change during the wait-list period, this analysis allows for a secondary estimate of treatment effect similar to a diamond response design [76]. Goldsmith et al. suggest that if the magnitude of the effect of the intervention is similar to that estimated through the comparison between groups during the 0 to 7 week period, then they may be pooled for a more precise estimate of treatment effect [76].

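### The Cook's-distance rule lets cases be dropped from the mixed model, conflicts with intention to treat, and leaves the primary result, the unit and n undefined

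*Protocol article*

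**What the plan says.** The Analysis section of the protocol article compares the groups with a linear mixed model at 0, 7 and 18 weeks, for the primary outcome (SMFA-DI) and the secondary outcomes. It counts the model's use of every available data point as an advantage and states: "Analysis will use intention-to-treat principles". It contains no deletion step.

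The Sensitivity analyses section names two analyses. The second begins: "If there are any cases removed from analysis due to a high influence on the mixed effects model". The cut-off is a Cook's distance above 4/n. If removal occurs, results with and without the influential points are compared.

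Three things are left open:
- which of the two fits is the primary result;
- whether the unit is a participant or a single visit (the sentence speaks first of *cases*, then of *points*);
- whether n counts participants (88 evaluable) or observations (3 × 88 = 264).

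**The concern.** In the sentence as written, removal comes first and the comparison follows from it. That foresees randomised participants, or some of their visits, leaving the mixed model because of their outcome values, which intention to treat is meant to prevent.

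Two statistical consequences follow.

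- **Error rate.** Deleting the largest residuals lowers the estimated residual variance, but the refitted group difference becomes no more precise. The standard error is then too small and p-values are too low, even with no true effect and with deletion that ignores treatment arm.
- **Estimate.** If benefit is concentrated in a minority, those participants have large residuals and are more likely to be deleted, which pulls the estimate towards zero.

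Cook's distance also belongs to a particular fitted model. Since the same type of model serves every outcome, each outcome could end up with a different analysed set. If the two fits fall on either side of P = 0.05, the plan does not say which one stands.

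**Working it through.** **Inputs (Sample size section).** Level and power: "The calculation was performed using a significance level of 0.05, a power of 0.8", taken as two-sided. Spread: "a standard deviation at each time-point of 23 points on the SMFA-DI". Correlations: "assuming a correlation between baseline and 7 weeks of 0.84"; "a correlation between baseline and 12 weeks of 0.82", read as the 18-week visit because there is no 12-week visit; and 0.84 between 7 and 18 weeks. Allocation is 1:1.

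**The plan's own figures.** The dropout step reproduces: 88/(1 − 0.20) = 110. The 88 does not reproduce from the listed inputs (a 2-df group-by-time test needs about 56 in total), but the contrast entered in the software is not stated and this does not affect the present point. The plan gives no error rate for the deletion rule. Its only benchmark is the nominal 5%.

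**How often the rule fires.** For deletion of a whole participant from the model with six group-by-visit means,

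D_i = q_i × n_g / [(n_g − 1)² × 6], where q_i = r_i′ Σ̂⁻¹ r_i

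Here r_i holds the participant's three residuals and n_g = 44. The multiplier is 44/(43² × 6) = 44/11,094 = 0.003966. For normal data q_i is roughly chi-squared with 3 df.

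- n = participants: the cut-off is 4/88 = 0.04545, so q_i > 0.04545/0.003966 = 11.46. The tail probability is about 0.9%.
- n = observations: the cut-off is 4/264 = 0.01515, so q_i > 0.01515/0.003966 = 3.82. The tail probability is about 28%.

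So the same rule removes either under one participant on average (0.8% × 88 ≈ 0.7) or about 24 (27% × 88), depending only on what n means. The percentages 0.8% and 27% are the simulated rates. Under the stricter cut-off, 46% of simulated null trials still flag at least one participant.

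**Type I error.** Trivariate normal data were generated with no true effect and no missing visits, N = 88. The group-by-time model was fitted, flagged units were removed, and the model was refitted. The 2-df group-by-time test was taken at 0.05. Participant-level rows use 20,000 runs; observation-level rows use 2,500 runs of a random-intercept REML model (Monte Carlo SE about 0.5 points near 5%).

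| Unit deleted | n in 4/n | Removed | All data kept | After removal |
|---|---|---|---|---|
| Participant | participants (88) | 0.8% of participants | 5.0% | 6.0% |
| Participant | observations (264) | 27% of participants | 5.0% | 18.3% |
| Observation | observations (264) | 4.8% of observations, touching 12% of participants | 5.5% | 16.6% |
| Observation | participants (88) | 0.05% of observations | 5.5% | 6.2% |

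With heavy-tailed data (t, 5 df), the first row becomes 5.1% to 6.5% and the second 5.1% to 13.0%. With N = 110, the participant-level results after removal are 6.2% and 18.4% (normal data).

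**Estimate.** The documents give no responder split, so this scenario is an assumption: 20% of the treated group improve by 30 points and the rest do not, a mean effect of 0.20 × 30 = 6 points. Participant-level deletion in the three-visit model with n = participants moves the average estimate from about 6.0 to about 5.6. A cut-off that deletes more participants would pull harder.

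**The case against.** The best defence is that the sentence is conditional, stands under a sensitivity heading, uses a numeric cut-off fixed in advance, and promises both fits. The section that defines the main analysis has no deletion step. The Blinding section keeps the analyst unaware of allocation.

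Much of this stands. A reader might infer that the plan makes the trimmed fit the headline result and relegates the full-data fit to a check. The text does not go that far: it does not rank them. Nor does the rule contradict the withdrawal section. The statement there that "data will be analyzed as a member of the group to which they were randomly assigned" concerns people who withdraw and says nothing about influential values. The conflict is with the intention-to-treat sentence in the Analysis section.

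A reader might also conclude that the rule doubles the false-positive rate. Single-visit models at 18 weeks do behave that way (change score 4.7% to 11.0%; ANCOVA 5.2% to 10.5%), but the trial plans a three-visit mixed model, so those figures should not size the problem.

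Two parts of the defence fail. Blinding limits selective removal by arm but does not stop the variance shrinkage, which needs no knowledge of allocation. Showing both fits exposes a disagreement but does not say which fit decides the trial.

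**Conclusion.** The point holds in limited form. The Sensitivity analyses section allows outcome-based removal from the mixed model, in conflict with intention to treat, and leaves the primary result, the unit and n unspecified. Under the plan's own SD and correlations, the cost is about one percentage point of type I error if participants are deleted with n = participants. It is about 12 to 13 points if n = observations (18.3 − 5.0 = 13.3 for participants; 16.6 − 5.5 = 11.1 for single visits, or about 12 against the nominal 5%). The observation-level reading with n = participants changes little, within Monte Carlo error.

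The figures assume complete data, no true effect and, for the main table, normal outcomes. The attenuation from about 6.0 to 5.6 points rests on an assumed responder share. Because the mildest readings do little harm and both fits are promised, this is a should-fix, not a fatal flaw. The conflict with intention to treat stands whichever reading is meant.

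**What to change.** Replace the second sensitivity analysis with wording such as:

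> The primary and secondary analyses include all available data from all randomised participants. No case is removed for influence; only verified data errors are corrected. As a sensitivity analysis only, the model is refitted without participants whose Cook's distance exceeds 4/n, where n is the number of participants.

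This settles the primary result, the unit and n together. It needs no new data and does not change the sample size. With all cases kept, the simulated type I error of the 2-df test is 5.0% (N = 88) to 5.2% (N = 110).

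The cost is that the headline p-value may be slightly less favourable than after trimming. The estimate itself could move either way, and in the responder scenario it would be larger with everyone kept. The article reports that recruitment was still under way at submission and that no preliminary analyses were planned, so at that stage the change could be made before results were seen.

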#### Protocol modifications

Any changes to protocol will be communicated with all study investigators and the Hamilton Research Ethics Board in writing. If there are any changes, the trial registry (clinicaltrials.gov) will be updated electronically. If the risks to participants change, all trial participants will be contacted directly by phone to communicate the change.

The population of people with barriers to accessing healthcare also poses a risk of higher attrition rates. For example, people with depression, substance abuse issues, and lower education are more likely to be lost due to failure to locate [79, 80]. The investigators have put in place measures to try to minimize the attrition rate, including asking for multiple methods of contacting the participant and planning to make multiple attempts to contact the participant for follow-up appointments.

Another limitation of this study design is the short-term follow-up before the wait-list group receives treatment. Estimating whether changes in function are maintained in the longer term (up to 36 weeks) will rely on within-group analysis of the treatment group. Given the lack of comparison, these results should be interpreted with caution. Changes at 25- and 36-week follow-up could be due to lasting treatment effects; however, period effects could also contribute to any long-term changes. Despite the limitations, the investigators considered it important to estimate the longer-term changes in function to inform future research on long-term efficacy.

Similarly, the comparison of the treatment period (weeks 18 to 36) with the wait-list period (weeks 0 to 18) in the wait-list group should be interpreted with caution given the lack of comparison group. Between-group comparisons performed during weeks 0 to 18 will provide a better estimate of treatment effect; however, the secondary estimate of treatment effect can add precision to effect estimates and allows investigators to estimate the impact of an 18-week delay before starting the self-management program. It is important that within-group changes are not be compared between groups as this has the potential to be misleading [81].

Treatment of chronic pain is a challenge [82, 83]. Improving function is frequently reported as an important outcome by people living with chronic pain [84], and reducing pain-related disability is important for reducing the financial burden [5–7]. Self-management represents an important opportunity to improve pain-related disability and ultimately the impact of chronic pain [85]. Unfortunately, existing evidence suggests chronic pain self-management support does not result in substantial changes in participant function [9, 10]. This study aims to evaluate a new approach to chronic pain self-management that targets function as the primary outcome. If this approach is demonstrates effectiveness, this could inform self-management programming to include greater focus on pain neurophysiology education and physiotherapist-led, individualized, goal-oriented exercise. By determining which factors help to predict an intervention response, practitioners will have valuable information on the prognosis of participants entering the program. Future research may help to develop tailored approaches to self-management for persons less likely to respond to this approach. Ultimately, this research could help to improve self-management for people with chronic pain.

The results of this trial will be published in peer-reviewed journals and presented at international conferences in the fields of pain and rehabilitation.

## Trial status

Recruitment started in September 2013. At the time of protocol submission, this study is recruiting patients.

### Dissemination

This study will be published in a leading journal and presented at international conferences in the field of pain and rehabilitation. A lay summary of results will be sent to study participants. Additionally, study results will be disseminated to clinicians through courses, presentations and workshops to a community of practice of physiotherapists in primary health care and a network of physiotherapists interested in the treatment of pain.

## Abbreviations

ANOVA: analysis of variance
COMMENCE: Chronic Pain Self-management Support with Pain Science Education and Exercise
IEQ: Injustice Experience Questionnaire
NFRS: Numeric Fatigue Rating Scale
NPQ: Revised Neurophysiology of Pain Questionnaire
NPRS: Numeric Pain Rating Scale
PCS: Pain Catastrophizing Scale
PHQ-9: 9-item Patient Health Questionnaire
PPT: Pressure Pain Threshold
PROMIS: Patient-reported Outcome Measurements Information System
PI: pain interference
PSEQ: Pain Self-efficacy Questionnaire
PTSD-C: Post-traumatic Stress Disorder Checklist - Civilian Version
SMFA: Short Musculoskeletal Function Assessment
DI: Dysfunction Index
BI: Bother Index
TSK: Tampa Scale of Kinesiophobia
WACHC: Woodstock and Area Community Health Centre
